## Abstract

**Background:**

There are theoretical grounds to suspect that heavy lifting at work is an important risk factor for ischemic heart disease (IHD). However the relationship has not been sufficiently acknowledged by empirical studies. Positive and statistically significant associations have been found in studies that utilize self-reported exposure data. Such studies are, however, prone to reporting bias. All else equal, people with a poor cardiovascular fitness/health may have a higher propensity to perceive their work environment as heavy.

**Objective:**

The study described in the present protocol aims to investigate the relationship between heavy lifting at work and IHD by use of material and methods that are free from reporting bias.

**Methods:**

This is a register-based prospective cohort study. Male blue-collar workers in Denmark will be identified and followed through national registers, from 2001-2010, for hospital treatment or death due to IHD. Relative rates of IHD between “workers in occupations likely to involve heavy lifting” and “other blue-collar workers” will be estimated through Poisson regression.

**Results:**

Results are expected to be ready in mid-2015.

**Conclusions:**

Since this is not a randomized study, it cannot confirm etiological hypotheses. It may, however, confirm that employment in occupations that involve heavy lifting is a predictor for IHD and thereby lend support to the hypothesis of a causal relationship.

## Introduction

### Background

A positive association between occupational physical demands, cardiovascular disease, and mortality has been found in several cohorts [1-8]. However, the specific types of occupational physical demands conferring the increased risk for cardiovascular disease remain unsettled [8].

A retrospective case-control study has indicated that occupational heavy lifting increases the risk for acute myocardial infarction while occupational walking and leisure time physical activity decrease the risk [3]. Moreover, in a recent prospective multi-adjusted study [9], men reporting heavy lifting at work had 55% increased risk for ischemic heart disease (IHD). Occupational heavy lifting has also been shown to impose an acute cardiovascular strain, excessively raising blood pressure for a prolonged period of time [2].

However, the two previous studies on the relationship between occupational heavy lifting and IHD may be biased by the self-reported measure of occupational heavy lifting. For example, it has been shown that people with myocardial infarction tend to remember and report previous physical activity levels differently than comparable control persons [10]. The largest recall bias was found for estimated associations between myocardial infarction and perception of occupational workload and repetitive or heavy lifting at work.

Therefore, studies investigating the risk for IHD among blue collar occupational groups likely to be involved in occupational heavy lifting compared with blue collar occupational groups not likely to be involved in occupational heavy lifting are needed.

### Objectives

The present study aims to investigate the relationship between heavy work and risk of IHD, among men in the general working population of Denmark.

The following hypotheses will be tested: (1) the rate of hospital treatment or death due to IHD is higher among blue-collar workers in occupations likely to involve heavy lifting than it is among blue-collar workers in occupations less likely to involve heavy lifting, and (2) the rate of death due to IHD is higher among blue-collar workers in occupations likely to involve heavy lifting than it is among blue-collar workers in occupations less likely to involve heavy lifting.

The above hypotheses are operationalizations designed to shed light on the following underlying hypotheses: (1) prolonged periods of occupational heavy lifting are likely to increase the risk of IHD, and (2) prolonged periods of occupational heavy lifting are likely to increase the risk of death due to IHD, either through an increased risk of occurrence or an increased risk of death given occurrence of the disease.

The hypotheses are based on the following theoretical arguments: heavy lifting is well known to acutely increase blood pressure. Several hours work per day of lifting-induced elevated blood pressure with minor possibilities for sufficient restitution may cause endothelial micro ruptures and damage of the arteries [1], inducing absorption of lipids and other pathogenic substances in the arterial wall leading to arteriosclerosis [11]. These conditions are associated with an increased risk of IHD [12].

## Methods

### Data Source

The study will use a database obtained through a record-linkage between four national registers—the central person register [13], the hospital patient register [14], the cause of death register [15], and the employment classification module. The central person register contains information on gender, addresses, and dates of birth, death, and migrations for every person who is or has been an inhabitant of Denmark sometime between 1968 and present time. A person’s occupation and industry are, since 1975, registered annually in the employment classification module. Since 1994, the occupations are coded according to the Denmark International Standard Classification of Occupations (DISCO-88) [16], which is a national version of the International Standard Classification of Occupations (ISCO-88). The national hospital register has existed since 1977 and contains data from all public hospitals in Denmark (more than 99% of all admissions). From 1977 to 1994, the register only included inpatients but from 1995 it also covers outpatients and emergency ward visits. Since 1994, the diagnoses are coded according to the International Classification of Diseases, 10th revision (ICD-10) [17].

The study will comply with The Act on Processing of Personal Data (Act No. 429 of 31 May 2000), which implements the European Union Directive 95/46/EC on the protection of individuals. The data usage is approved by the Danish Data Protection Agency, journal number: 2001-54-0180. According to Danish law, questionnaire and register-based studies do not need approval by ethical and scientific committees, nor informed consent.

### Occupational Categories

The occupational categories to be used in the hypothesis tests are given, in terms of DISCO-88 codes, in Table 1. The occupations considered to be strongly associated with heavy lifting were selected in accordance with expert opinion by [name], National Research Centre for the Working Environment (NRCWE). The opinion of [name] was seconded by [name] [name], University of Southern Denmark. The selection was done in connection with the design of an earlier study, which would investigate the association between heavy lifting and retinal detachment. Data from the Danish work environment cohort survey (DWECS) in the year 2000 [18] were used to confirm that the occurrence of heavy lifting among male workers who belong to [name]’s group is significantly higher than it is among workers who belong to the other occupational category. Responses to the following questions were considered: (1) How much of your time at work do you carry or lift objects? (Almost all the time; Approximately 3/4 of the time; Approximately 1/2 of the time; Approximately 1/4 of the time; Rarely/very little; Never), and (2) How much does what you carry or lift typically weigh? (Less than 3 kg; 3-10 kg; 11-29 kg; 30-49 kg; 50 kg or more).

The proportion who reported that they carry or lift objects approximately one-quarter of the time or more was statistically significantly higher among males in [name]’s group than it was among other blue-collar workers. The same holds for the ones who reported that they carry or lift objects approximately one-quarter of the time or more and that the objects typically weigh 30 kg or more.

**Table 1 table1:** Occupational categories according to DISCO-88.

Occupational category	DISCO-88
**[name]’s group (occupations that are strongly associated with heavy lifting)**	
	712. Building frame and related trades workers
	921. Agricultural, forestry and fishery laborers
	931. Construction laborers
	933. Transport and storage laborers
**Other blue-collar workers (occupations in which heavy lifting is less likely to occur)**	
	All workers with a first digit DISCO-code equal to 6 (agricultural trades workers), 7 (craft and related trades workers), 8 (plant and machine operators and assemblers), or 9 (elementary occupations). Except those that belong to [name]’s group.

### Statistics on Lifting, Smoking, and BMI

We know that a high body mass index (BMI) and smoking are important risk factors for IHD. Unfortunately, the data material of the present study does not contain individual-based information on these factors. We have, however, individual-based data on a random sample (ca. 1 per 400) of our study population (DWECS 2000), which we can use to evaluate the possible influence of the two risk factors. In Table 2, we give estimated percentages of occupational lifting, by occupational group. We also give statistics on BMI and smoking habits.

As seen in Table 2, the proportion of overweight workers was significantly lower among workers in [name]’s group than it was among other blue-collar workers. To get an idea of the extent that this factor may influence the rate ratio of IHD between the two groups, we calculated the expected rate ratio under the assumption that the groups are equal in all respects other than the BMI distribution. According to our calculations, the expected rate ratio, E[RR], for IHD ([name]’s group vs other blue-collar workers) equals 0.96 (95% CI 0.91-1.01) under the assumption that the groups are equal in all respects other than the BMI distribution. The standard error of the logarithm of the estimate equals 0.0274. The standard error and the confidence interval are based on Gauss propagation of error formulas. The point estimate is based on the following equation:

E[RR]=(1+p_1_(RR_1_−1) + p_2_(RR_2_−1)) / ((1+q_1_(RR_1_−1) + q_2_(RR_2_−1))

where RR_1_is the rate ratio for IHD among people in the category 25≤BMI< 30 vs BMI< 25 and RR_2_is the rate ratio between the categories BMI≥30 and BMI<25. The p_i_’s are the proportions in the various BMI categories in [name]’s group while the q_i_’s are the proportions among other blue-collar workers. The proportions were estimated through DWECS 2000, while the rate ratio for IHD, by BMI group, was estimated on workers registered in DWECS 1990, 1995, 2000, and 2005 through a follow-up (1991-2009) in the national registers described in the Methods section. The estimated rate ratio for IHD, by BMI category is given in Table 3.

**Table 2 table2:** Percentage of male workers exposed to occupational lifting, smoking, and high body mass index (BMI) according to DWECS 2000, by occupational category.^a^

Exposure category	[name]’s group n (%)	Other blue-collar workers n (%)	OR	95% CI
Lifting ≥¼ of work hours	206 (79.2)	512 (47.7)	4.17	3.02-5.76
Lifting ≥¼ of work hours (“The objects weigh typically 30 kg or more.”)	43 (16.5)	114 (10.6)	1.67	1.14-2.44
BMI ≥25	113 (43.7)	574 (53.8)	0.66	0.50-0.87
BMI ≥30	25 (9.7)	116 (10.9)	0.88	0.56-1.38
Current smoker	118 (45.4)	481 (45.0)	1.02	0.78-1.34

^a^The total number of observations varied (due to missing values) between 259 and 260 in [name]’s group and between 1067 and 1073 among other blue-collar workers.

**Table 3 table3:** Rate ratio (RR) with 95% confidence interval (CI) for hospital treatment or death due to IHD, 1991-2010, by body mass index (BMI) in a representative sample of Danish employees.^a^

BMI	Persons	Person years	Cases	RR	95% CI
<25	7078	89,514	180	1.00	-
25≤ BMI< 30	4059	41,564	186	1.41	1.14-1.74
≥30	1244	10,454	87	2.69	2.08-3.49

^a^The analysis was controlled for gender, age, and calendar time.

### Statistics on Other Occupational Exposures

In the last section, we looked at BMI and smoking. In this section, we will look at statistics on certain work environmental factors, which theoretically may influence the rate of IHD. The following occupational exposures have been associated with an increased risk for subsequent IHD: noise [19], poor decision latitude [20], high job insecurity [21], shift work [22], prolonged working hours [23], and air pollution [24].

These factors are not as influential as BMI—being obese versus normal weight increases the risk with almost 200%, while the various work environmental exposures typically are associated with an elevated risk of between 5 and 25% [19]. Nevertheless, if we find that the rate of IHD is significantly higher in “occupations that are strongly associated with heavy lifting” than in “occupations in which lifting is less likely to occur”, then we want to rule out the possibility that the result is due to an increased exposure to other work environmental risk factors.

DWECS 2000 does not provide any reliable measure of exposure to air pollution. It contains, however, questions that can be used to obtain measures of the other above mentioned risk factors. In Table 4, we give estimated percentages of exposure to noise, poor decision latitude, high job insecurity, shift work, and prolonged working hours, by occupational category.

A person was categorized as exposed to:

loud noise, if he replied “Approximately 1/4 of the work hours” or more to the question “Are you subjected to noise that is so loud that you have to raise your voice in order to talk to others?” He was categorized as unexposed if he replied “Rarely/very little” or “Never”poor decision latitude, if he replied “Rarely” or “Never/Almost never” to the question “Do you have a significant influence in the decision making at your work?”high job insecurity, if he answered “Yes” to any of the following questions: “Are you worried about becoming unemployed?” or “Are you worried about difficulties in finding a new job with your present qualifications?”prolonged working hours, if he worked 41 hours or more per weekshift or night work, if the normal placement of his work was either fixed at night or shifting (working on two shifts, three shifts, or irregularly during the day/week according to special schedule or rotation). He was categorized as unexposed if he replied “Fixed day duty”, “Fixed morning duty”, or “Fixed evening shift/evening work”.

**Table 4 table4:** Percentage of male workers exposed to loud noise, low decision latitude, high job insecurity, prolonged working hours, and shift or night work, according to DWECS 2000, by occupational category.^a^

Exposure category	[name]’s group n (%)	Other blue-collar workers n (%)	OR	95% CI
Loud noise ≥¼ of work hours	116 (44.6)	463 (43.2)	1.06	0.81-1.39
Poor decision latitude	76 (29.2)	331 (30.0)	0.92	0.68-1.24
High job insecurity	62 (26.4)	311 (32.2)	0.76	0.55-1.04
Prolonged working hours	46 (17.7)	318 (29.9)	0.50	0.36-0.71
Shift or night work	22 (8.5)	216 (20.2)	0.37	0.23-0.58

^a^The total number of observations varied (due to missing values) between 235 and 260 in [name]’s group and between 967 and 1072 among other blue-collar workers.

### Study Design

The study population consists of all male inhabitants of Denmark, who at baseline (January 1, 2001) were 21-59 years old and belonged to any of the two occupational groups given above. These people will be followed in our national registers, from January 1, 2001 to December 31, 2010. Approximately half a million working men will be included in the study.

The following clinical endpoints will be considered: (1) hospital treatment or death with IHD as principal diagnosis/cause of death (the case definition includes these ICD-10 codes: I20 angina pectoris, I21 acute myocardial infarction, I22 subsequent myocardial infarction, I23 certain current complications following acute myocardial infarction, I24 other acute ischemic heart diseases, I25 chronic ischemic heart disease), and (2) death with IHD as principal cause of death.

The study population will be followed, first for death or hospital treatment due to IHD and then for death due to IHD. Only those who were free from IHD-related hospital visits throughout the calendar year preceding baseline will be included in the analysis.

For each of the two endpoints, each of the included individuals will be followed until any of the following events occur: he reaches the clinical endpoint of the follow-up, he emigrates, he dies, or the study period ends. Person years at risk (PYRS) will be calculated for each individual.

We will use Poisson regression to estimate rate ratios between [name]’s blue-collar workers and all other blue-collar workers, while adjusting for age (10-year age groups). The rate ratios will be presented with 95% confidence intervals. PROC GENMOD in SAS version 9.3 will be used to implement the analysis.

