### Hypothesis Testing Criteria

A hypothesis is confirmed (regarded as statistically significant) if the lower boundary of the 95% confidence interval of its associated rate ratio exceeds one. The significance level is thereby set at .025.

If the first hypothesis is confirmed and the rate ratio of the second hypothesis exceeds one, then we will conclude that the first of the underlying hypotheses is supported by the data. If the second hypothesis is confirmed, then we will conclude that the second of the underlying hypotheses is supported by the data.

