### Power Calculations

A 10-year follow-up (2001-2010), including all economically active men in Denmark aged 21-59 years in January 2001, yields ca. 420 cases of hospital treatment or death due to IHD per 100,000 person years, and 23 cases of death due to IHD per 100,000 person years. At baseline, 8.73% (112,699/1,291,665) of the workforce belonged to [name]’s group while 31.38% (405,385/1,291,665) belonged to the group “other blue-collar workers”. If we assume that the number of cases is proportional to the number of people in the various job groups, then the expected numbers of cases of hospital treatment or death due to IHD are approximately 4650 in [name]’s group and 16,000 among the other blue-collar workers. The corresponding numbers for death due to IHD are 255 and 880.

With the above data as input, the statistical powers of the tests are given as a function of the true rate ratio in Figure 1. The calculations are based on the Poisson distribution, the propagation of error formulas, and the central limit theorem.

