## Discussion

### Study Protocol

With this study protocol, we define the hypotheses, inclusion criteria, statistical models, and test criteria completely before we look at any relationship between the exposure and outcome variables in our data. By doing so, we have eliminated hindsight bias. The prospective design and the exclusion of prevalent cases ascertain that the exposure takes place before the outcome. The size of the study gives us a tremendous statistical precision and, since we are dealing with registers that cover the entire population of Denmark, we do not have any problems with sampling bias, response bias, or volunteer bias.

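### Age is adjusted only in 10-year groups although dates of birth are held: residual confounding of roughly 0–2.5%, direction unknown, against a 3.3% half-width for the first endpoint

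*Protocol article*

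**What the plan says.** Under Study Design, the protocol article states "We will use Poisson regression to estimate rate ratios between" the heavy-lifting group and all other blue-collar workers, "while adjusting for age (10-year age groups". Age is the only covariate named. The cohort is men "who at baseline (January 1, 2001) were 21-59 years old", followed "from January 1, 2001 to December 31, 2010". Sensitivity Analysis 1 changes only the censoring (at age 60). Sensitivity Analysis 2 changes only who is included and otherwise keeps the primary design. The age term is therefore the same in all three.

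Under Data Source: "The central person register contains information on gender, addresses, and dates of birth, death, and migrations for every person". Finer age is thus already in the linked data.

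Under Hypothesis Testing Criteria, a hypothesis is confirmed when the lower 95% limit is above one: "The significance level is thereby set at .025". The Discussion says that the statistical models are completely defined in advance and adds: "The size of the study gives us a tremendous statistical precision".

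**The concern.** Age is a strong predictor of IHD. At an assumed rise of 6–10% per year, the rate grows about 1.8-fold to 2.6-fold across ten years (1.06^10 = 1.79; 1.10^10 = 2.59). A 10-year age term removes differences between bands but none within them. If the two groups differ in age inside a band, that difference passes into the rate ratio, and a larger cohort does not shrink it. In a smaller study, a residual of 1–2% would be lost in sampling error. Here the first endpoint is estimated so precisely that such a residual can change the result of the test. No planned analysis would reveal it.

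**Working it through.** **Inputs from the protocol (Power Calculations).** "8.73% (112,699/1,291,665) of the workforce belonged to" the heavy-lifting group, and 405,385 men belong to the comparison group. Rates are 420 (hospital treatment or death) and 23 (death) per 100,000 person-years. Expected cases are 4650 and 16,000 for the first endpoint, and 255 and 880 for IHD death.

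**Check of the stated counts.** 112,699 × 10 × 420/100,000 = 4733 and 405,385 × 10 × 420/100,000 = 17,026 before any loss of follow-up. The stated 4650 is within 3%; the stated 16,000 is 6% lower. Scaling 4650 by group size gives 4650 × 405,385/112,699 = 16,726. Using this instead of 16,000 leaves the half-width at about 3.3%, so the stated counts are used below.

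**Precision.**
- First endpoint: SE(log RR) = √(1/4650 + 1/16,000) = 0.01666; 1.96 × SE = 0.0327; exp(0.0327) = 1.033. An observed ratio just above 1.033 confirms hypothesis 1.
- IHD death: SE = √(1/255 + 1/880) = 0.0711; 1.96 × SE = 0.139, or about +15%/−13%.

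**Assumptions (not in the protocol).** The IHD rate rises by g = 6–10% per year of age. Ages in the comparison group are uniform from 21 to 59. The age distribution of the exposed group is tilted exponentially to give a chosen difference in mean age. The true ratio is 1, everyone is followed for 10 years, and bands start at age 20. The Poisson model has one term per age band.

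**Residual bias, exposed men older (g = 6% to 10%):**

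| Difference in mean age | 10-year, attained age | 10-year, baseline age | 5-year, either basis | Single-year baseline age |
|---|---|---|---|---|
| 1 year | 0.3–0.4% | 0.4–0.6% | 0.1–0.2% | 0 |
| 2 years | 0.6–0.9% | 0.7–1.2% | 0.2–0.3% | 0 |
| 4 years | 1.2–1.7% | 1.5–2.5% | 0.3–0.6% | 0 |

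If exposed men are younger, the sizes are nearly the same with the sign reversed. If the age structures match, the bias is zero. A 4% bias appears only with a difference in mean age of about 6–8 years, baseline bands and g of 8–10%.

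**Same point by within-band age gap.** Bias = (1 + g)^d − 1, where d is the gap in years. A 2.5% bias needs d = ln(1.025)/ln(1 + g) = 0.42 years at g = 6% and 0.26 years at g = 10%. The full 3.3% half-width needs 0.56 and 0.34 years.

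**Effect on the test of hypothesis 1** (normal approximation, SE 0.01666):
- Upward bias, true ratio 1: the false-positive rate is 1 − Φ(1.96 − ln(1 + bias)/SE). It goes from 2.5% to 8.6% at 1%, 22% at 2% and 32% at 2.5%.
- Downward bias, true ratio 1.05: power is Φ(ln(1.05 × factor)/SE − 1.96). It goes from 83% to 64% at factor 0.99 and 40% at 0.98.
- Downward bias, true ratio 1: the false-positive rate falls to 0.5% at factor 0.99 and below 0.1% at 0.98.

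**IHD death:** an upward bias of 1% or 2% raises the false-positive rate only to 3.4% or 4.6%.

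**The case against.** The 10-year grouping is explicit and prespecified, and nothing in the protocol contradicts it. Sex and broad social class are handled by restriction to male blue-collar workers. The protocol reports neither IHD rates by age nor age by group, so every bias figure rests on assumed inputs. Small age gradients between the groups (0.5–1% per year in the exposed-to-comparison ratio) leave only 0.2–0.8%. The protocol's own estimate for BMI, an expected ratio of 0.96 with a standard error of 0.0274 on the log scale, is as large or larger and more uncertain than the sampling error. Finer age would therefore not by itself make a 3% excess interpretable. Support for the first underlying hypothesis also requires the death ratio to exceed one. All of this stands and limits the weight of the point.

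Two stronger readings do not hold. A reader might infer a bias of up to 4%; that needs an extreme age difference that the protocol does not show. A reader might also infer that the coarse bands will produce a false confirmation. The usual argument, that men leave heavy jobs earlier, makes exposed men younger within bands. That biases the ratio downward, against the hypothesis, and costs power. Inflation of the false-positive rate needs exposed men to be older within bands, and the protocol gives no ground to expect either pattern. Its remark on early retirement concerns age 60 and over, whereas exposure is fixed at baseline in men under 60.

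The objection does not supply a reason for coarse bands when dates of birth are held. The BMI gap cannot be closed with these data; the age gap can.

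**Conclusion.** The point holds as a should-fix and a free improvement. Under an assumed 6–10% yearly rise in the IHD rate and differences in mean age of up to about 4 years, 10-year groups can leave roughly 0–2.5% of residual age confounding in the first-endpoint ratio, against a 3.3% half-width. Size and direction cannot be determined from the protocol. The consequence is lost power if exposed men are younger within bands, or an inflated false-positive rate if they are older. For IHD death the point is minor. It concerns the width of the age bands only and does not show that the planned result would be wrong.

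**What to change.** In the primary model and both sensitivity analyses, replace the 10-year age groups by single years of age or a spline of exact age, or at the least by 5-year bands. State whether age is baseline or attained. Make the change before any exposure–outcome result is seen, since the protocol relies on having fixed its models in advance. The cost is one sentence and one changed model term. No new data are needed, and with 4650 + 16,000 = 20,650 expected cases the loss of precision is negligible. A table of age by group would also show how much the change matters.
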